#### Statistical considerations

In order for the study findings to maximally impact practice and policy, they will need to be adequately powered to detect differences in outcomes of interest to each of the stakeholders (patients, clinicians, shared decision-making research experts, and healthcare payers). We will have sufficient funding to enroll 930 patients, accounting for a loss to follow-up rate as high as 5% (there was 2% lost to follow-up in our pilot trial)
[11], we anticipate having complete data on 884 patients. Table 
1 shows the anticipated power we will have to detect differences in each of the patient and stakeholder-important outcomes on completion of the trial.

**Table 1 T1:** Anticipated power to detect patient and stakeholder-important outcomes on completion of the trial

**Outcome (n = 884)**	**Usual Care***	**Decision Aid***	**Difference**	**Power**
**Patient knowledge**	44% (23.3)	60% (20.9)	16% (9.5%, 22.5%)	99%
**Patient engagement in the decision-making process (n = 221)**	7.0 (5.5)	26.3 (8.2)	19.3 (18.4, 20.2)	99%
**Decisional conflict†**	35.9 (18.9)	22.3 (21.1)	13.6 (11.0, 16.2)	99%
**Trust in the physician**	79.3 (19.9)	83.4 (19.8)	4.1 (1.5, 6.7)	86%
**Patient satisfaction with the decision made (% agree or strongly agree they are satisfied)**	69.7 (25.6)	80 (25.6)	10.3 (4.6%, 16.0%)	99%
**Safety (major adverse cardiovascular events)‡**	0%	0%	0% (−−)	78%
**Proportion of patients admitted for cardiac testing**	77%	67%	10% (4.1, 15.9)	90%
**Healthcare utilization**	8.3 (0.8)	7.0 (0.7)	1.3 (1.2, 1.4)	99%

*Estimates were determined from our completed pilot randomized trial [11].

†Lower decisional conflict scores indicate less conflict experienced by patients related to feeling uninformed.

‡Non-inferiority, one-sided test with alpha = 0.05 with a maximum difference of 5%.

We will use standard techniques appropriate for patient-randomized trials, with each outcome compared between study arms using t-tests for continuous outcomes and chi-square tests for dichotomous outcomes. Rather than assume the intervention effect is independent of the study site where the patient is seen or of the clinician who sees them, we will assess intra-site and intra-clinician correlations. We will then stratify all tests on the study site unless the intra-clinician correlation is non-trivial, in which case we will stratify on a clinician basis. We will calculate differences and their confidence intervals using standard techniques for continuous and dichotomous data. If there are differences in baseline characteristics between the two study groups, these will be accounted for using regression models that will include an indicator for study arm. Finally, we will analyze clinician surveys using regression models with robust standard errors to account for the repeated measures on clinicians.

Descriptive analyses will be performed to describe any potential heterogeneity of treatment effect (HTE) and facilitate synthesis of subgroup results in future meta-analyses. We will conduct descriptive HTE analyses by age, gender, race/ethnicity, quantitative pre-test probability of ACS, level of education, OPTION scores, and study site. The outcomes assessed with HTE analyses will be the same as those assessed in the trial (such as knowledge, engagement, satisfaction, and healthcare utilization). We will also conduct interaction testing to determine the interaction between the decision aid and each pre-specified characteristic.

Resource use will be compared both descriptively and using multivariable models. Descriptive comparison for 30-day utilization will utilize the Wilcoxon rank-sum test to account for the skewness of the outcome measures. The multivariable models for resource utilization will be estimated using the two-part or one-part negative binomial or log gamma regression models. A two-part model will be utilized for outcomes where more than 10% of the subjects have a zero outcome measure. The covariates in the multivariable models will include factors that may not be accounted for in the randomization such as comorbidities and severity of illness. Comorbidities will be measured using the Elixhauser method, which is a commonly used measure for the acute setting
[29]. We will also analyze the results using a subset of patients who primarily receive their entire healthcare at the participating centers. We expect that this analysis will provide a sensitivity analysis of the overall trial results based on self-report.

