#### Randomization

Patients will be randomized after informed consent is obtained and it is confirmed that all inclusion and no exclusion criteria are met, prior to the patient-clinician discussion of treatment options and patient risk. Allocation will be concealed by means of an online password-protected randomization algorithm designed using Medidata Balance™ Medidata Solutions, New York City, USA. Patients will be dynamically stratified
[19] by enrolling by site, age and sex because of the known association of age and sex with cardiovascular risk and the availability of these data at the time of enrollment. Allocation will be based on a 1:1 ratio between the intervention and usual care arms. Though we will not be able to blind patients and clinicians to use of the decision aid, we will blind the investigators and individuals not involved in providing care to the patient allocation.

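### Table 1's interval for the primary outcome (9.5% to 22.5%) is a two-proportion interval that contradicts the standard deviations in its own row, which give about 13.1 to 18.9 points

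*Protocol article*

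**What the plan says.** All references are to the Protocol article. Under Statistical considerations, the primary outcome row of Table 1 reads "Patient knowledge 44% (23.3) 60% (20.9) 16% (9.5%, 22.5" (percent), with power 99%. A footnote to the column headings says "Estimates were determined from our completed pilot randomized trial". The table header gives n = 884, and the text above it says "we anticipate having complete data on 884 patients". The Randomization section says "Allocation will be based on a 1:1 ratio between the intervention and usual care arms", so 442 per arm are expected.

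On analysis, Statistical considerations plans "using t-tests for continuous outcomes and chi-square tests for dichotomous outcomes" and adds: "We will calculate differences and their confidence intervals using standard techniques for continuous and dichotomous data".

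The Outcome measures section describes knowledge as assessed by a post-visit survey that covers several topics: short-term risk, implications of testing, management options and radiation. The article does not say in words whether the result is a mean score or a yes/no classification.

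**The concern.** A row that prints a value with an SD in each arm describes a continuous measure. The interval beside it should then follow from those SDs and the sample size. Here it is much wider than they allow, so the row combines inputs for one kind of endpoint with a precision statement for another.

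What is at stake is the accuracy of the only precision figure the article gives for its primary outcome, and whether a reader can tell which branch of the analysis rule (t-test or chi-square) applies to it. The design itself is not at stake.

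**Working it through.** **Inputs.** Knowledge 44% (SD 23.3) versus 60% (SD 20.9), Table 1. Complete data on 884 patients (930 × 0.95 = 883.5), Statistical considerations. 1:1 allocation, Randomization, hence 442 per arm. Table 1 states no confidence level for this row; 95% two-sided is assumed, and other rows reproduce at that level.

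**Step 1: reproduce the printed interval.** Treat 44% and 60% as proportions of patients:

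- SE = √[(0.44 × 0.56 + 0.60 × 0.40)/442] = √(0.4864/442) = 0.0332
- 0.16 ± 1.96 × 0.0332 = 0.16 ± 0.0650, i.e. **9.5% to 22.5%**, exactly as printed.

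Close variants do not match: pooled variance gives 9.41 to 22.59, a continuity correction 9.27 to 22.73, and 465 per arm 9.66 to 22.34.

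**Step 2: use the row's own SDs.**

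- SE = √[(23.3² + 20.9²)/442] = √(979.70/442) = 1.49 points
- 16 ± 1.96 × 1.49 = 16 ± 2.92, i.e. **13.1 to 18.9 points**.
- Ratio of half-widths: 6.50/2.92 = 2.23.

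No obvious alternative rescues the printed figure from these SDs. The pilot size (204 patients) gives 9.93 to 22.07, a total of 221 patients gives 10.16 to 21.84, the 99% level gives 12.17 to 19.83, and the 99.9% level gives 11.10 to 20.90.

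**Step 3: could the SDs belong to a yes/no outcome?** A binary outcome has SD √[p(1 − p)], i.e. 49.6 points at 44% and 49.0 at 60%. The printed 23.3 and 20.9 are less than half of that, so they cannot describe one yes/no result per patient.

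**Step 4: compare the other rows at 442 per arm.**

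| Row | SDs printed? | Printed interval | Means formula | Proportion formula |
|---|---|---|---|---|
| Decisional conflict | yes | 11.0, 16.2 | 10.96, 16.24 | – |
| Trust | yes | 1.5, 6.7 | 1.48, 6.72 | – |
| Utilization | yes | 1.2, 1.4 | 1.20, 1.40 | – |
| Admission | no | 4.1, 15.9 | – | 4.12, 15.88 |
| **Knowledge** | yes | 9.5, 22.5 | 13.08, 18.92 | 9.50, 22.50 |
| **Satisfaction** | yes | 4.6, 16.0 | 6.92, 13.68 | 4.62, 15.98 |

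Knowledge and satisfaction are the two rows that carry SDs but print the proportion interval. The engagement row has a separate fault: it is labelled n = 221, but its printed 18.4 to 20.2 is what 442 per arm gives (18.38 to 20.22). With 221 in total the result is 17.46 to 21.14.

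**Step 5: power at 442 per arm (two-sided 5% assumed).** Knowledge: above 99.9% by the means formula and 99.8% by the proportion formula, so the printed 99% stands in substance. Satisfaction: above 99.9% by the means formula but 94.3% by the proportion formula. Its printed 99% therefore fits the SDs, while its printed interval fits the proportions.

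**The case against.** The strongest reply is that nothing depends on this cell. The text says "We will have sufficient funding to enroll 930 patients, accounting for a loss to follow-up rate as high as 5" percent, so funding sets the sample size, not precision. Table 1 is about power, the knowledge power is right under either formula, and the error makes the trial look less precise than it would be. All of this stands, and it limits the point to a correction of the table.

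It is also fair that the article never assigns knowledge to the continuous or the dichotomous branch. The score reading is inferred from the SDs, though strongly. If knowledge were a yes/no outcome, the interval would be right and the SDs wrong. The row is inconsistent either way.

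A reader might go further and infer any of three things that the article does not support:

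- **That the proportion formula will be used in the results.** The text plans "each outcome compared between study arms using t-tests for continuous outcomes" and intervals matched to the type of data. Nothing indicates that a score would be analysed as a proportion.
- **That the 9.5-point lower limit restricts what the trial can conclude.** It is a planning projection from pilot values; conclusions will rest on the observed data.
- **That most of the sample is wasted.** These SDs would indeed reach ±6.5 points with about 89 patients per arm (1.96² × 979.70/6.5²), but a misprinted projection loses no information.

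**Conclusion.** The point holds as an internal inconsistency in the primary outcome row. The printed interval is the two-proportion interval at 442 per arm, whereas the row's SDs and the t-test rule give about 13.1 to 18.9 points, so the printed half-width is about 2.2 times too wide. The error is conservative and leaves the knowledge power and the planned sample size unchanged. The satisfaction row mixes the two formulas in the same way, and there the choice does affect power: about 94% against the printed 99% if it is a proportion.

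This rests on equal arms of 442, a two-sided 95% level, and the SDs being those of a per-patient score. The figure of 13.1 to 18.9 is unadjusted; it does not reflect the planned stratification by site or clinician, and neither does the printed interval.

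**What to change.** - **Knowledge row.** State that knowledge is analysed as a mean percent score, label the row accordingly, and replace the interval with 16 points (13.1, 18.9), unadjusted. Keep power at 99%. If knowledge is in fact a yes/no outcome, remove the SDs, keep 9.5% to 22.5%, and say that the chi-square test applies.
- **Satisfaction row.** Choose one data type. As a proportion, which its label suggests, remove the SDs, keep 4.6 to 16.0 and change power to about 94%. As a mean score, relabel the row and print 6.9 to 13.7, keeping 99%.
- **Engagement row.** While the table is open, reconcile its interval with its stated n of 221.

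The cost is a few table cells, row labels and one sentence of text. No new patients, data or design change is needed.

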**Figure 3 F3:**
[figure not shown]
**Decision aid that includes the option of coronary CT angiography.** This version of the decision aid was developed for use at the University of Pennsylvania emergency department (Pennsylvania, United States) in which coronary CT angiography is frequently used in lieu of cardiac stress testing.

Participating clinicians were trained by means of a one-hour grand rounds presentation given by the lead investigator at each participating site, as well as a training video that demonstrated use of the decision aid in a simulated patient encounter. The lead study coordinator at the central coordinating site trained each of the study coordinators at the participating sites to ensure comprehension of the study protocol and the standardized execution of study procedures. As was done in our pilot trial, study coordinators will offer to provide the treating clinician a concise refresher of the content included in the decision aid at the time of patient enrollment. Videos of the patient-clinician disposition discussion will be obtained to assess the fidelity of the use of the decision aid in the intervention group and to monitor for contamination in the control group. Video and audio recordings will be consented to separately and are not required for participation in the trial.

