#### Data collection

Data documenting the process of screening for potentially eligible participants, application of the eligibility criteria (including the reason for each exclusion), the variables entered into the pretest probability calculator, the arm to which each patient is randomized, and other information best collected in real time will be recorded by study coordinators using a standardized case report form (Additional file
2). Patients’ preferences for understanding numerical information and their preferred approach to participation in medical decision-making will be assessed by a survey administered prior to the clinical encounter (Additional file
3).

Immediate post-visit surveys will collect data on patient knowledge, decisional conflict, patients’ trust in their physician, and patient satisfaction with the decision made (Additional file
4). The degree to which clinicians engage patients in the decision-making process will be assessed by having two trained team members independently review videos of the clinician-patient disposition discussion and apply the OPTION scale
[21].

The patient will be contacted 45 days after enrollment via telephone (primary method of contact) for assessment of safety. If the primary method of contact is not successful the study coordinator will subsequently contact the patient utilizing a secondary method of contact specified by the patient at the time of consent (such as email, a secondary phone number, or mail) for a follow-up assessment. Safety will be assessed using a standardized phone follow-up script to determine whether a MACE occurred and, if so, the date of the event (Additional file
5). Events occurring within 45 days will be recorded to ensure consistency with the duration of follow-up used in the development of the QPTP instrument
[15] and MACE within 30 days will be reported in accordance with standardized reporting guidelines for risk stratification studies of ED patients with potential ACS
[26].

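### The engagement (OPTION) row of Table 1 is labelled n = 221, but its interval is computed on all 884 patients and is half as wide as 221 patients would give

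*Protocol article*

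**What the plan says.** Table 1 is headed n = 884, in line with the text above it: "we anticipate having complete data on 884 patients". One row overrides that number and is labelled "Patient engagement in the decision-making process (n = 221"). It assumes a mean (SD) of 7.0 (5.5) under usual care and 26.3 (8.2) with the decision aid, a difference and interval of "19.3 (18.4, 20.2"), and power of 99%.

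Engagement is a secondary outcome measured with the OPTION scale. Under Data collection, scoring is done by having "two trained team members independently review videos of the clinician-patient disposition discussion and apply the OPTION scale". Under Refinement of the decision aid, after the Figure 3 legend, the article states: "Video and audio recordings will be consented to separately and are not required for participation in the trial".

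On allocation, the Randomization section says "Allocation will be based on a 1:1 ratio between the intervention and usual care arms". On analysis, Statistical considerations names "t-tests for continuous outcomes and chi-square tests for dichotomous outcomes", with standard confidence intervals for differences. The article states neither a confidence level for Table 1 nor how 221 was obtained.

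**The concern.** A row with its own, smaller sample size should have an interval based on that sample size. An interval of less than one point either side looked too narrow for about 110 patients per arm with standard deviations of 5.5 and 8.2. If it was carried over from the full-trial calculation, the row contradicts itself.

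Two things are at stake. The stated precision for engagement would be better than the design can deliver. The reader also could not tell whether engagement is to be measured in the whole trial or in a quarter of it (221 = 884/4). That matters beyond this cell, because the article plans descriptive subgroup analyses and interaction tests with engagement among the outcomes, including by site.

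**Working it through.** **Inputs.** From Table 1: SDs 5.5 and 8.2, difference 19.3, row n = 221, table n = 884. From Randomization: 1:1 allocation. Assumption: two-sided 95% intervals, since no level is stated (tested in step 3).

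**Formula.** With m patients per arm, SE = √((5.5² + 8.2²)/m) = √((30.25 + 67.24)/m) = √(97.49/m). The interval is 19.3 ± 1.96 × SE.

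**Step 1: reproduce the printed interval.** With 884 patients, m = 442:
- SE = √(97.49/442) = 0.470
- half-width = 1.96 × 0.470 = 0.92
- interval 18.38 to 20.22, which rounds to the printed 18.4 to 20.2.

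Working backwards, limits that round to 18.4 and 20.2 need a half-width between 0.85 and 0.95. Since m = 1.96² × 97.49 / (half-width)², that means about 415 to 518 patients per arm.

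**Step 2: use the row's own sample size.**

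| Reading of 221 | m per arm | SE | Half-width | 95% interval | Half-width relative to 0.92 |
|---|---|---|---|---|---|
| Total | 110.5 | 0.939 | 1.84 | 17.46 to 21.14 | 2.0 |
| Per arm | 221 | 0.664 | 1.30 | 18.0 to 20.6 | 1.4 |

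Neither reading gives the printed interval. The factor of 2.0 is √(884/221). Using t quantiles for 221 in total moves each limit by only 0.01 (17.45 to 21.15).

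**Step 3: test the 95% assumption on other rows, at 442 per arm.**
- Decisional conflict: 13.6 ± 1.96 × √((18.9² + 21.1²)/442) = 13.6 ± 2.64, or 10.96 to 16.24 (printed 11.0 to 16.2).
- Trust: 4.1 ± 1.96 × √((19.9² + 19.8²)/442) = 4.1 ± 2.62, or 1.48 to 6.72 (printed 1.5 to 6.7).
- Utilization: 1.3 ± 1.96 × √((0.8² + 0.7²)/442) = 1.3 ± 0.10, or 1.20 to 1.40 (printed 1.2 to 1.4).
- Admission: 10% ± 1.96 × √((0.77 × 0.23 + 0.67 × 0.33)/442) = 10% ± 5.9%, or 4.1% to 15.9% (as printed).

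These rows follow one convention: 95% with 442 per arm. The engagement interval follows it too, despite its own label.

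**Step 4: power.** At 221 in total the difference is 19.3/0.939 = 20.5 standard errors, so power stays above 99%.

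**Step 5: effect on the by-site estimates.** If the five sites enrolled equally (an assumption), 221 scored encounters give 221/5 ≈ 44 per site, or about 22 per arm, and a half-width of 1.96 × √(97.49/22.1) ≈ 4.1 points. With 884 there would be about 88 per arm and site, and a half-width of about 2.1.

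**The case against.** The strongest objection is about weight. Table 1 exists to show power, and the power for this row does not change. Engagement is secondary, no sample size or decision rule rests on the interval, and the trial will compute its own interval from its own data. This stands, and it limits the point to a table correction.

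A second objection is that the origin of 221 is inferred. No sentence links it to consent for recording. Being exactly a quarter of 884, it could equally be a planned one-in-four scoring sample. The Usual care section and the Discussion also suggest that recording is intended widely in both arms. This stands in part. The article does not say where 221 comes from, and it should. But OPTION is scored only from video and video is optional, so the row concerns recorded encounters on either explanation.

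A third is that 221 might be a number per arm, or might itself be the slip. The header's 884 is a total and the row replaces it with a quarter of that figure, so a total is the natural reading. Read per arm, the interval is still too narrow. If 884 was meant, the label is wrong instead. In no case can label and interval both stand as 95% figures.

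Finally, one standard error either side at n = 221 (18.36 to 20.24) also rounds to the printed limits. The rows checked above are 95% intervals, so this is very probably a coincidence. It would not be a 95% interval in any event.

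**Conclusion.** The concern holds. The engagement interval was computed on the full 884 patients and does not belong to the row's n = 221. At 221 in total the 95% interval is 17.5 to 21.1, twice as wide as printed. The conclusion rests on a 95% level, which the other rows support, on equal arms, and on reading 221 as a total. The consequence is small: the stated precision of one secondary outcome is wrong and the size of its analysis set is unclear, while the 99% power stands.

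**What to change.** In the engagement row of Table 1, replace the interval with 17.5 to 21.1 and keep n = 221 with its split, about 110 per arm. Add a footnote saying that the row covers recorded encounters only, so that engagement is reported as an estimate in patients who consented to recording, and saying how 221 was arrived at (expected recording consent or a planned scoring sample).

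If the investigators meant 221 per arm, the interval is 18.0 to 20.6 and the label should say so. If they meant all 884, the label must change and be reconciled with recording being optional.

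The cost is one corrected cell and one footnote. The stated precision becomes less favourable. Power, sample size and trial conduct do not change.

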#### Outcome measures

When selecting outcome measures we obtained input from a patient and caregiver representative, clinicians (emergency medicine clinicians and cardiologists), researchers (health services researchers and shared decision-making experts), and a payer representative (Chief Medical Officer of Mayo Clinic Health Solutions). In face-to-face meetings with the patient and caregiver representative it became clear that knowledge was the outcome that was of greatest interest to the patient, so patient knowledge was selected as the primary outcome. Thus, as we did in our pilot trial, we will assess patient’s knowledge regarding their short-term risk for ACS, the potential implications of cardiac testing, the available management options, and the potential risk of radiation exposure through a post-visit survey administered immediately after the clinical encounter
[11].

We will also assess a number of secondary outcomes, including patient engagement in the decision-making process, as measured by the OPTION (observing patient involvement) scale
[21]; the degree of conflict patients experience related to feeling uninformed, as measured by the Decisional Conflict Scale (DCS)
[22]; trust in the physician measured via the Trust in Physician Scale (TPS)
[23]; patient satisfaction with the decision made, via a Likert scale on the post-visit survey; and safety as determined by the prevalence of Major Adverse Cardiac Events (MACE) within 30 days of the ED visit.

Consistent with recommendations in a recently published consensus document on ACS research in emergency departments
[24], we will define MACE as AMI
[25], death due to a cardiac or unknown cause, emergency revascularization, ventricular arrhythmia, or cardiogenic shock. We will exclude MACE that occurs during the index admission to the ED but rather focus on events occurring after discharge, in the outpatient setting, which could have potentially been avoided or diagnosed in the ED or hospital. This approach avoids having to adjudicate whether MACE occurring in the ED or hospital were ‘missed’ based on a post-hoc review of potentially incomplete medical records. We will collect data on all MACE that occur up to 45 days from the index ED visit as this is the follow-up interval assessed by the QPTP instrument

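### The satisfaction row of Table 1 contradicts itself: its label, its SD of 25.6, its interval and its 99% power cannot all be right

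*Protocol article*

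**What the plan says.** The outcome measures section of the protocol article lists, among the secondary outcomes, "patient satisfaction with the decision made, via a Likert scale on the post-visit survey". It mentions no dichotomy there.

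Table 1 (Statistical considerations) labels the row "Patient satisfaction with the decision made (% agree or strongly agree they are satisfied". The row reads 69.7 (25.6) for usual care, 80 (25.6) for the decision aid, a difference of 10.3 (4.6%, 16.0%), and 99% power. The bracketed figures are laid out like the SDs of the trust and decisional conflict rows. The two clearly binary rows, admission and major adverse events, carry no bracketed figure in the arm columns.

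The text below the table assigns "t-tests for continuous outcomes and chi-square tests for dichotomous outcomes". On sample size it says "we anticipate having complete data on 884 patients", and the randomization section says "Allocation will be based on a 1:1 ratio between the intervention and usual care arms". Alpha is stated only for the safety row, in a footnote: "Non-inferiority, one-sided test with alpha = 0.05 with a maximum difference of 5" (per cent).

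**The concern.** The label describes the share of patients who endorse satisfaction, so each patient contributes a yes or a no. The SD of such an outcome follows from the percentage itself and cannot be 25.6 points at 69.7% or 80%. Either the label or the SD is therefore misplaced, and the power or the interval is wrong with it.

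Two things depend on the answer. Table 1 is the article's evidence that each stakeholder outcome is adequately powered, and this row may overstate its power. The plan also ties the choice of test to whether an outcome is continuous or dichotomous, so the conflict leaves the test for satisfaction open.

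**Working it through.** **Inputs.** From Table 1: 69.7 and 80, SD 25.6 in each arm, difference 10.3, interval 4.6 to 16.0, power 99%. From the sample-size text: 930 × 0.95 = 883.5, printed as 884, so 442 per arm at 1:1. Two-sided alpha of 0.05 is my assumption and is tested in step 5.

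**1. Reproducing the 99%.** Treat the row as two means with SD 25.6.
- SE = 25.6 × √(2/442) = 1.722.
- Power = Φ(10.3/1.722 − 1.96) = 99.997%. The decisional conflict row, which also computes to practically 100%, is printed as 99% too, so this matches.
- The interval from the same SE is 10.3 ± 1.96 × 1.722 = 6.9 to 13.7, which is not the printed one.

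**2. Reproducing the interval.** Treat the row as two proportions.
- SE = √[(0.697 × 0.303 + 0.80 × 0.20)/442] = 0.02898.
- Interval = 0.103 ± 1.96 × 0.02898 = 4.62% to 15.98%. This is the printed 4.6% to 16.0%.

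**3. SD of a binary outcome.**
- √(0.697 × 0.303) = 46.0 points and √(0.80 × 0.20) = 40.0 points.
- Working back from the printed interval, the half-width of 5.7 implies a common SD of 5.7/1.96/√(2/442) = 43.2 points.

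**4. Power for the row as labelled** (69.7% against 80%, 442 per arm, two-sided 0.05).

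| Method | Power |
|---|---|
| Unpooled variance: Φ(0.103/0.02898 − 1.96) | 94.5% |
| Arcsine | 94.4% |
| Pooled variance under the null | 94.3% |
| Simulated chi-square | 94.3% |
| Continuity-corrected | 93.3% (simulated 93.4%) |

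With no loss to follow-up (465 per arm), the pooled figure is 95.3%. None of these reaches 99%.

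**5. Is two-sided 0.05 a fair assumption?** Compare other rows of Table 1.

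| Row | Printed | Two-sided 0.05 | One-sided 0.05 |
|---|---|---|---|
| Trust | 86% | 86.7% | about 92% |
| Admission | 90% | 91.3% pooled, 90.0% continuity-corrected | about 95% |
| Satisfaction as a proportion | 99% | 93.3% to 94.5% | 97.1% |

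Two-sided testing fits the trust and admission rows and one-sided testing does not. Even one-sided, satisfaction as a proportion stays below 99%.

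**6. Does the interval show which reading is meant?** Check the knowledge row: 44% (23.3) against 60% (20.9), printed interval 9.5% to 22.5%.
- Binomial: 1.96 × √[(0.44 × 0.56 + 0.60 × 0.40)/442] = 6.5 points, giving 9.5 to 22.5. This is the printed interval.
- From its SDs: 1.96 × √[(23.3² + 20.9²)/442] = 2.9 points, giving 13.1 to 18.9.

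So the table gives a binomial interval to another row that carries SDs. A binomial interval in the satisfaction row is therefore no proof that satisfaction is a proportion.

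**The case against.** The best counter-argument is that satisfaction may be a mean score after all. The outcome measures section names a Likert scale and no cut-point. The arm cells carry no percent sign, as in the trust and decisional conflict rows, while the clearly binary rows do. The knowledge row shows that the authors put a binomial interval beside SDs elsewhere in the table. On that reading the SD and the 99% are correct, and only the label and the interval are wrong. This stands as a live possibility. The figures are said to come from the pilot trial, and the document gives nothing further from it to decide the matter. It does not clear the row, because two of its entries would still need correction.

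A reader might infer that the true power is 93% to 94% and that 99% is simply false. The document does not support that as a settled conclusion: it holds only if the label is taken at its word. A reader might also infer that the trial is underpowered for satisfaction. That does not follow, since power exceeds 90% on both readings.

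The consequence is also fairly called small. Satisfaction is secondary and the planned enrolment is tied to funding.

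**Conclusion.** The inconsistency is certain; which entry is at fault is not. Taken as labelled, with the chi-square test that the plan assigns to dichotomous outcomes, the row has about 93% to 94% power rather than 99%. The chance of missing the assumed difference is then about 6% to 7%, not 1%. Taken as a mean score, the 99% holds, but the label is wrong and the interval should be 6.9 to 13.7.

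The lower power rests on 442 analysable patients per arm and on two-sided alpha of 0.05, which is assumed for this row. One-sided 0.05 would give 97.1%. That the SD of 25.6 produced the 99% is inferred from the reproduction; the article does not say so. This is a minor reporting error with one practical loose end, namely which test applies to satisfaction.

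**What to change.** State whether satisfaction is analysed as a proportion or as a mean score, and make the row agree.

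- **If a proportion:** delete (25.6) from both arm cells, keep 4.6% to 16.0%, and restate power as about 93% (continuity-corrected) or 94% (uncorrected).
- **If a mean score:** relabel the row as a mean score, keep the SD of 25.6 and the 99%, and correct the interval to 6.9 to 13.7.

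In either case, state the alpha and sidedness used for the superiority rows of Table 1. The cost is one table row and one line of text, with no change in enrolment. If satisfaction is a proportion, the stated power becomes slightly less favourable.
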